### Randomization

We created seven pairs of zones that were matched on the basis of socioeconomic conditions and estimates of the number of sex workers and women who use AOD residing in them. These estimates were based on inputs from our outreach workers who had worked on one of our prior studies that reached drug-using, at-risk women and sex workers in the Pretoria area [23–25].

We randomized zones within each pair to the control arm or the intervention arm. Each participant’s study arm is determined by the zone in which she was recruited.

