#### Sample size and power

The sample size was lowered to 600 from 1050 as originally planned. The original sample size was calculated on the basis of an anticipated HIV prevalence of 30%; however, HIV prevalence in the sample is 55%. Accordingly, the smaller sample (n = 600) will allow for the identification of a clinically meaningful effect with sufficient statistical power, while accounting for logistical difficulties, including a citywide study, limited structural resources, increased costs, and other factors outside the control of the study. We assume 14 clusters, approximately 30 observations per cluster and 20% attrition, yielding a final sample size of about 480 respondents at 12-month follow-up. This allows us a medium to strong likelihood of detecting an effect of the intervention assuming a strong effect (based on Cohen’s beta of 0.6). This would translate to an approximately 10% to 15% difference in the outcomes for any behavioral outcome (e.g., reductions in AOD use, number of instances of unprotected sex). We would not be able to detect mild to weak effects in analyses that consider the mediation of the effect of the intervention through some cognitive outcome, such as intentions/self-efficacy/knowledge/gender power. The reduction in power also greatly reduces the likelihood of testing whether the intervention yielded modification effects across the levels of some covariate and mediational effects as well. However, we will examine the distribution of the variables and reestimate power given the final sample size and variance estimates. No outcome or mediator/moderator analyses will be conducted unless there is strong power (e.g., Beta greater than .8, for a 2-tailed test and p = .05).

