#### Analysis

We will first conduct descriptive statistical analysis of baseline variables and clinical characteristics of the two intervention arms to examine the extent, if any, of baseline or clinical imbalances between the two arms using contingency table analyses (Mantel-Haenszel for categorical and analysis of variance for continuous variables). The analysis will center around estimating the impact of the intervention on each of the primary study outcomes, observed at baseline and 6- and 12-month follow-up visits, using all available cases consistent with an intent-to-treat method. In addition to evaluating changes in each outcome by intervention arm at 6-month follow-up, the analysis will examine whether the changes are sustained or decay at 12-month follow-up. Given the longitudinal nature of the data, our primary analytic strategy will apply a generalized estimating equation (GEE) modeling approach to account for the multiple dependencies of repeated measures collected on the same individuals over time, and the clustering of the outcomes by community. Because the communities may range from 5 to 100 cases, the generalized linear/nonlinear mixed model (e.g., hierarchical linear modeling or multilevel modeling with random effects) would likely face problems with convergence given the heterogeneity in the variation between communities. Therefore, we opt for a statistical strategy that treats this level of clustering as a nuisance parameter, and thereby estimating the population-averaged effects of the outcomes for subjects sharing the same profile of individual and community-level characteristics. For outcomes with binomial or count distributions, the logit link will be specified to obtain effect estimates of the magnitude of differences between arms within each follow-up visit. For continuously distributed outcomes, an identity link function will be specified. We expect that we will estimate the working correlation matrix at the temporal level using a first-order autoregressive structure (AR-1) and an exchangeable correlation matrix at the community-level, thereby allowing the subjects within each cluster to be constrained to equality but freeing the estimates between clusters.

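### Read literally, the planned GEE gives each of the 14 zones its own correlation, and the arm comparison at a follow-up visit would then reject far more often than 5% under no effect

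*Protocol article*

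**What the plan says.** The Analysis section of the protocol article states that "our primary analytic strategy will apply a generalized estimating equation (GEE) modeling approach". Over time it expects an AR-1 working correlation. For women of the same community it expects an exchangeable one, "thereby allowing the subjects within each cluster to be constrained to equality but freeing the estimates between clusters". The effect it names for binary outcomes is the arm difference at each follow-up visit on the logit scale. It also plans to look at change from baseline to 6 months and at whether that change lasts to 12 months. It warns of very uneven zones: "Because the communities may range from 5 to 100 cases".

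The design has few clusters. The Randomization section says "We randomized zones within each pair to the control arm or the intervention arm", with seven pairs, so there are 7 zones per arm.

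**The concern.** If something is equal within a cluster and its estimates are freed between clusters, the plain sense is one correlation parameter per zone. A zone has many women but only one zone mean, so its own correlation is in effect the squared distance of that mean from the fitted arm mean. The model then trusts the zones that happen to agree with the fit and discounts the rest. The robust variance is computed from the same down-weighted residuals, so much of the between-zone variation against which a cluster-randomized comparison must be judged drops out.

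At stake is the validity of the between-arm test on condom use, the primary outcome. A correction of the standard error alone would not restore it.

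**Working it through.** **Inputs from the protocol article**

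- Test level (Sample size and power): "for a 2-tailed test and p = .05".
- Size (same section): "We assume 14 clusters, approximately 30 observations per cluster and 20% attrition, yielding a final sample size of about 480 respondents at 12-month follow-up", from 600 enrolled ("The sample size was lowered to 600 from 1050 as originally planned").
- Allocation: 7 against 7 zones, randomized within pairs.
- Zone sizes: 5 to 100.

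**The plan's own figure.** 600 × (1 − 0.20) = 480, which reproduces. That is 480 / 14 = 34.3 women per zone. The stated 30 per zone would give 14 × 30 = 420. This does not affect the present point, and about 480 was used.

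**Assumptions.** The article gives no ICC, outcome rate or exact size profile. ICCs of 0.01 to 0.05 are shown, with outcome rates of 0.5 or 0.3. Zones were either 4 to 80 women (5 to 100 less 20%) or equal at 34. The standard error is taken to be the usual robust (sandwich) one.

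**Step 1: the weight of a zone.** For zone i with n women, mean ȳ and fitted arm mean μ, let e be the Pearson residual (y − μ)/√[μ(1 − μ)]. The moment estimate from that zone alone is

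ρ_i = [(Σe)² − Σe²] / [n(n − 1)].

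With Σe² ≈ n this gives

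1 + (n − 1)ρ_i ≈ n(ȳ − μ)² / [μ(1 − μ)].

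The zone's weight n / [1 + (n − 1)ρ_i] is then about μ(1 − μ)/(ȳ − μ)². It depends on the zone's own deviation and hardly on n.

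**Step 2: illustration** with n = 34 and μ = 0.5 (zone means chosen for the example):

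- ȳ = 0.52: 34 × 0.0004 / 0.25 = 0.054, so ρ is negative. Set to 0, the weight is 34.
- ȳ = 0.60: 34 × 0.01 / 0.25 = 1.36, weight 34 / 1.36 = 25.
- ȳ = 0.70: 34 × 0.04 / 0.25 = 5.44, weight 34 / 5.44 = 6.25.

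Three zones of equal size thus get weights of 34, 25 and 6.25.

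**Step 3: null simulation.** Rejection at nominal two-sided 5%, robust z-test, negative zone correlations set to 0 (the least inflating choice). The three-visit model has AR-1 within woman plus a zone-level exchangeable correlation, and the figures are for the arm difference at 6 or 12 months (1,000 trials per setting). The single-visit model has 2,500 trials per setting.

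| ICC | Three visits, zone-specific | Three visits, common | One visit, zones 4–80, zone-specific | One visit, equal zones, zone-specific |
|---|---|---|---|---|
| 0.01 | 25–26% | 11% | 36–37% | 34% |
| 0.02 | 31% | 10–11% | 43–45% | 39–40% |
| 0.05 | 38–40% | 10–12% | 53% | 48–49% |

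Repeat single-visit runs with separate code put the upper end at 56%. With a common correlation the single-visit test rejects 8–13%. In the three-visit model, freeing the correlation therefore adds about 14 points (25.4 − 11.0) to 28 points (39.8 − 12.2). Allowing negative zone correlations makes it worse.

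**Step 4: does a better standard error repair it?** In the single-visit model with a Mancl-DeRouen correction and t on 14 − 2 = 12 df, zone-specific correlations still reject about 20–37% at ICC 0.01–0.05. A common correlation with the same correction rejects about 3–5%. This correction was not examined in the three-visit model.

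**Step 5: precision.** In the single-visit model at ICC 0.02 the SD of the log odds ratio is 0.256 with a common correlation and 0.325 with zone-specific ones. (0.256 / 0.325)² = 0.62, so about 38% of the information is lost.

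**Step 6: change from baseline.** For the arm-by-visit contrast with a time-constant zone correlation, rejection is 10–14% under either structure. Freeing adds nothing there.

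**The case against.** The strongest reply is that the article never meant 14 correlations. It speaks of one exchangeable matrix for communities and treats clustering as a nuisance. The disputed words come after a connective that presents them as a consequence of choosing an exchangeable structure, so they may be a loose gloss on ordinary GEE: one shared value within zones, and zones unrelated to each other. The whole sentence is given as an expectation, and a condensed article may leave the parameterization to a fuller plan.

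Part of this stands. The intention cannot be settled from the text, and the error rates above apply only under the literal reading. But independence between zones means fixing a between-zone correlation at zero, which is the opposite of freeing an estimate. The section also cites differing variation between communities as its reason for avoiding mixed models, which makes the literal reading easy to reach. The article does not leave the structure open. It describes one, in words that an analyst could follow into an invalid test.

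A reader might also infer that the trial's whole primary analysis, on every outcome, would show false positives at these rates. The documents do not support that. The section also plans change-from-baseline comparisons, which freeing does not make worse. Only binary outcomes were simulated, whereas continuous and count outcomes are planned too. And about 10–12% rejection in the three-visit model comes from the uncorrected robust standard error with 14 zones, not from this clause.

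**Conclusion.** The concern holds in conditional form. If the clause is followed as written, the test of the arm difference at a follow-up visit on a binary outcome rejects in about 25–40% of null trials in the three-visit model and about 34–56% in the single-visit model, at assumed ICCs of 0.01–0.05. The baseline for comparison is about 8–13% with a common correlation and the same standard error, and the remainder is due to freeing the correlation. The exact rates rest on the assumed ICC, outcome rate and zone sizes. The direction does not: in the single-visit model the excess appeared at every ICC tried from 0 to 0.10, and with equal as well as unequal zones. If the authors meant only that zones are independent, the model is sound in this respect and the sentence misdescribes it.

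**What to change.** Replace the clause with: *a single exchangeable zone-level correlation, common to all 14 zones, with different zones assumed independent*. State alongside it a small-sample-corrected robust standard error with t on 12 df, because the common correlation alone still rejects about 8–13%. The same wording serves whichever meaning was intended.

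The cost is a sentence or two in the analysis plan, with no further participants or data. The common-correlation model is the simpler and standard fit and, in the single-visit simulation, gave the more precise estimate. P-values will be less favourable than under the literal reading, which is the purpose of the change.

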#### Outcome measures

The primary outcome is self-reported male or female condom use during the participant’s most recent episode of vaginal or anal intercourse. Other outcomes include frequency of condom use, frequency and quantity of alcohol use, urine drug screen results for illicit substance use, and frequency of violent victimization (physical or sexual). Additional outcomes for women living with HIV include receiving HIV treatment, ART adherence, and CD4 counts. Analyses for HIV-RNA viral load on stored dried blood spots at follow-up may occur at a later date.

Alcohol use is measured biologically with a breathalyzer test and through self-report. A biological urine drug screening test determines recent use of a panel of substances, including cannabis/marijuana, opioids, cocaine, methamphetamine, and Mandrax (methaqualone). Victimization includes self-report of being beaten, attacked with a weapon, or forced to have sex during the previous 90 days. We assess if women living with HIV received treatment and took ART both biologically and by self-report. Self-report for ART refers to being prescribed ART, taking ART if prescribed, and missing any doses in the past 30 days. We also examine measures of adherence included in the U.S. National Institute on Drug Abuse’s harmonization initiative [30]. To help interpret these data, we also collect self-reports of barriers to ART use.

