In addition to the main outcome analyses, we will examine the mechanism of change via standard mediational models. For this approach, we will lag the timepoints such that the baseline will be the most exogenous, then the midpoint 6-month observation will be the mediator and the 12-month observation will serve as the distal outcome. We can also estimate a mediational model with two timepoints, estimating the distal outcome at 6 months along with the concurrent mediator. These models will be fit using standard structural equation modeling software packages (e.g., Mplus), which can adjust the standard errors via bootstrapping to reduce bias and also remove exogenous measurement error. These models can be estimated using a mixture of distributions, such as a categorical mediator or outcome in concert with a continuously distributed mediator or outcome. The mediational analyses will address the extent to which the intervention worked and estimate the direct and indirect mechanisms. However, moderational analyses will address the extent to which the intervention worked for specific subgroups, such as women who are HIV positive, women in a relationship, and women with a criminal history. For these analyses, interaction terms will be created by multiplying the effect of the intervention by the moderator variable of interest.

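### The optional 6-month mediation model takes mediator and outcome from the same interview, so it cannot support the mechanism reading that the article gives it

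*Protocol article*

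**What the plan says.** The article (Analysis) puts baseline first in its main mediation model, "then the midpoint 6-month observation will be the mediator and the 12-month observation will serve as the distal outcome". It goes on: "We can also estimate a mediational model with two timepoints", that is, "estimating the distal outcome at 6 months along with the concurrent mediator". One interpretation then covers both models: "The mediational analyses will address the extent to which the intervention worked and estimate the direct and indirect mechanisms". Nothing marks the second model as exploratory or mentions reverse causation.

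The timing of the outcomes is in Outcome measures. The primary outcome is condom use at the "most recent episode of vaginal or anal intercourse". Victimization covers being beaten, attacked with a weapon or "forced to have sex during the previous 90 days". For drugs, "A biological urine drug screening test determines recent use of a panel of substances". The mediators appear only as examples of a cognitive outcome in Sample size and power, "such as intentions/self-efficacy/knowledge/gender power". That section also makes any mediator analysis conditional on adequate power.

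**The concern.** An indirect effect has a mechanistic meaning only if the mediator changed before the outcome. The lagged model respects that order. In the two-timepoint model, the last sexual episode and the 90-day window are already past when the woman answers questions about her self-efficacy or intentions. A woman who recently used a condom may for that reason report more self-efficacy. A woman who tends to give favourable answers may do so on both scales. Either process correlates mediator and outcome within arm, and the model reads that correlation as the path from mediator to outcome.

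At stake is the explanation of an effect, not its existence. The trial could report that the intervention works through, say, self-efficacy when self-efficacy only followed the behaviour. Bootstrapped standard errors and removal of measurement error, which the article mentions, do not address direction. Nor does the power condition: more power makes a spurious path easier to detect.

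**Working it through.** **Plan's own figure.** The article states no figure for the mediation models. Its sample size gives the n for the check: 600 × (1 − 0.20) = 480, as stated, or 240 per arm.

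**Inputs from the article:** 480 women; a difference of 10 or 15 percentage points; two-sided 5% level.

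**Assumed inputs:** 40% condom use in control; equal arms; no clustering; the same 480 women at both visits; mediator residual SD of 1; reverse effect d of the outcome on the mediator, in those SD units. The true effect of the mediator on the outcome is zero throughout.

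**General formula.** Let Y = τT + u with var(u) = 1, and M = rY + e with var(e) = 1 − r². The fitted arm-to-mediator path is a = rτ, the fitted mediator-to-outcome path is b = r, and a × b = r²τ. The false share of the total effect is therefore r².

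**Binary outcome.** Let v be the within-arm variance of Y, and M = dY + e with var(e) = 1. The false share is then d²v / (1 + d²v). For 40% against 55%, v = (0.40 × 0.60 + 0.55 × 0.45) / 2 = 0.244.

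**Scenario 1: the mediator moves only because of the past outcome.** The simulation used 2,000 runs and counted a false positive when both paths were significant.

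| d | Formula | Simulated share | False positives, 10 points | False positives, 15 points |
|---|---|---|---|---|
| 0 | 0% | 0% | 0.2% | 0.4% |
| 0.3 | 0.022 / 1.022 = 2.1% | 2.2% | 5% | 7% |
| 0.5 | 0.061 / 1.061 = 5.7% | 5.9% | 8% | 13% |
| 0.8 | 0.156 / 1.156 = 13.5% | 13.1% | 12% | 23% |
| 1.0 | 0.244 / 1.244 = 19.6% | 19% to 20% | 17% | 30% |

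**Scenario 2: the intervention also raises the mediator by 0.3 SD, 15-point difference.** Now a = 0.3 + 0.15d, b = dv / (1 + d²v), and the share is ab / 0.15. For d = 0.3: a = 0.345, b = 0.073 / 1.022 = 0.072, and 0.345 × 0.072 / 0.15 = 16%.

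| d | Simulated share | False positives |
|---|---|---|
| 0 | about 0% | 3% to 5% |
| 0.3 | 16% | 87% |
| 0.5 | 29% | 98% |
| 0.8 | 47% | 99% |

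**Scenario 3: no reverse effect, but a shared trait or reporting tendency.** The arm effect on the mediator is again 0.3 SD and the difference 15 points. One SD of the trait moves the mediator by 0.5 or 1.0 and the outcome probability by 0.075 or 0.15. The false share is 6% or 15%, with 28% or 65% false positives.

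**The lagged model under Scenario 2.** If 6-month behaviour does not carry over to 12 months, the false share is 0.0% to 0.3% and false positives are 4% to 5%. With an assumed persistence of 0.3 and no adjustment for the 6-month outcome, the false share is 5% to 14% and false positives are 16% to 65%, for d from 0.3 to 0.8. Adjusting for the 6-month outcome removes this by construction, because in this set-up the 12-month outcome depends only on arm and the 6-month outcome.

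**The case against.** The second model is optional, the article commits itself first to the lagged one, and the power condition may mean that neither is run. This stands and limits the weight of the point. It does not change how the model would be read if it were run.

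The article gives no mediator instrument or recall period, so the order of measurement is inferred. Order of recording is also not causal order: the two intervention sessions are 3 to 5 days apart, so self-efficacy could have shifted months before the last sexual episode, with the 6-month score standing in for that earlier state. This too stands. It shows that the concurrent model might reflect mechanism. It does not show that the model can tell mechanism from consequence.

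Four stronger readings are tempting and are not supported:

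- **The outcome precedes the mediator for every outcome.** It does for condom use at last sex and 90-day victimization, and in effect for urine-detected drug use. CD4 count is measured at the visit, and alcohol partly so by breathalyzer; there the order is merely not established.
- **A quarter or a third of the effect would be spurious through reverse causation alone.** The r² formula gives 25% and 36% at r = 0.5 and 0.6. With a binary outcome at 40%, d = √[r² / (1 − r²) / 0.24], so these need reverse effects of √(0.333 / 0.24) = 1.18 SD and √(0.5625 / 0.24) = 1.53 SD, beyond the range simulated.
- **The trial would credit an intervention component that did nothing.** The mediators are cognitive states, and the trial compares the whole package with control. In these scenarios the total effect is real and only its explanation is wrong.
- **The lagged model is free of the problem.** Under persistence it is biased too, though less. Its covariates are ordinarily left to the analysis plan, so their absence from the article is not an error.

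**Conclusion.** The point holds for an optional, secondary model. For outcomes recalled from before the interview, the concurrent 6-month model cannot separate mechanism from consequence or shared reporting, yet the article reads it as it reads the lagged model. The false share is about 2% to 20% for assumed reverse effects of 0.3 to 1.0 SD acting alone, and 16% to 47% for 0.3 to 0.8 SD if the intervention also raises the mediator by an assumed 0.3 SD. The shares depend on the assumed reverse effect, arm effect on the mediator and control rate. The false-positive rates depend also on 480 women and on ignoring clustering. None of this shows that spurious mediation will occur, only that the model could not reveal it. The primary GEE estimate of the intervention effect is unaffected.

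**What to change.** In the Analysis section, base mechanism claims only on the lagged model (arm, 6-month mediator, 12-month outcome), adjusted for baseline mediator and baseline outcome. State that the 6-month concurrent model, if run, is exploratory and reports an association between mediator and outcome, with no indirect effect and no statement about mechanism. The model need not be deleted.

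Adjustment of the lagged model for the 6-month outcome suits a sensitivity analysis. It removes carry-over bias but also blocks genuine mediation that runs through 6-month behaviour, so neither version is clearly right alone.

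The cost is small: a change of label for one optional model, and covariates from the baseline visit, provided the mediators were asked then, which the article implies but does not state. There are two real downsides. Mechanism claims would rest on women with a 12-month visit, about 480 of 600 if attrition is as planned. They may also miss a mechanism whose effect has faded by 12 months, a decay that the Analysis section itself allows for.

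### The mediation paragraph names bootstrapping as its only standard-error device and does not carry over the clustering by the 14 randomized zones

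*Protocol article*

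**What the plan says.** All references are to the protocol article.

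- **Randomization.** There are seven matched pairs of zones. "We randomized zones within each pair to the control arm or the intervention arm". Arm does not vary within a zone: "Each participant’s study arm is determined by the zone in which she was recruited".
- **Analysis, first paragraph.** The outcome models are GEEs, chosen to "account for the multiple dependencies of repeated measures collected on the same individuals over time, and the clustering of the outcomes by community". An exchangeable working correlation at community level is named for these models. Mixed models are set aside because convergence problems are expected with very unequal communities.
- **Analysis, second paragraph.** Mediation is to be studied with standard models in SEM software such as Mplus, "which can adjust the standard errors via bootstrapping to reduce bias". No zone term, cluster-robust standard error, multilevel model or resampling of zones is mentioned. The resampling unit is not given. The paragraph says these models will show how far the intervention worked and by which direct and indirect routes. It then describes moderation by interaction terms, again without mention of zones.
- **Sample size and power.** "We assume 14 clusters, approximately 30 observations per cluster and 20% attrition", "yielding a final sample size of about 480 respondents at 12-month follow-up". Mediator and moderator analyses are to be run only if power, re-estimated at the end, is strong.

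**The concern.** The clustering provision is written for the GEE, and the mediation analysis leaves the GEE. The one standard-error device then named does not, as ordinarily applied, deal with dependence between women in the same zone: a default bootstrap draws women as if they were independent. Because arm is constant within a zone, the information on an arm-to-mediator path, or on a direct arm-to-outcome path, comes from 7 zones against 7 zones, however many women each contains.

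If women were resampled, intervals for these paths would be too narrow and a mechanism could be reported that reflects only zone-to-zone variation. The plan itself expects communities to differ, since this is part of its argument against mixed models.

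**Working it through.** **Inputs from the article:** 14 zones in 7 pairs; about 480 women at 12 months; zones that may hold 5 to 100 women; two-sided 5% level.

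**Assumed, because the article gives no figure:** an ICC of 0.01 to 0.10, and a coefficient of variation (CV) of zone size of about 0.63. The ICC is the between-zone share of variance that matters for the arm contrast. If the pair matching removes part of it, a lower row of the table applies.

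**Step 1, the plan's own figure.** 600 × (1 − 0.20) = 480, so the final sample is reproduced. The stated cluster size does not lead there: 14 × 30 = 420, or 336 after 20% attrition. The check therefore uses 480 / 14 = 34.3 women per zone. The conclusion does not depend on this choice: at 30 per zone the error rates below become 8%, 12% and 21% for ICC 0.01, 0.02 and 0.05.

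**Step 2, formulas.**
- Design effect: DE = 1 + ((1 + CV²) × m − 1) × ICC
- Naive standard error / true standard error = 1/√DE
- Actual two-sided error at nominal 5% = 2 × (1 − Φ(1.96/√DE))

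**Step 3, equal zones (m = 34.3, CV = 0).** For ICC 0.02: DE = 1 + 33.3 × 0.02 = 1.67, √DE = 1.29, understatement = 1 − 1/1.29 = 23%, error = 2 × (1 − Φ(1.52)) = 13%.

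| ICC (assumed) | DE | Standard error too small by | Actual error of a 5% test |
|---|---|---|---|
| 0 | 1.00 | 0% | 5% |
| 0.01 | 1.33 | 13% | 9% |
| 0.02 | 1.67 | 23% | 13% |
| 0.05 | 2.66 | 39% | 23% |
| 0.10 | 4.33 | 52% | 35% |

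**Step 4, unequal zones (CV 0.63).** (1 + 0.63²) × 34.3 − 1 = 46.9. DE is then 1.47, 1.94 and 3.35 for ICC 0.01, 0.02 and 0.05, and the error is 11%, 16% and 28%.

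**Step 5, simulation of one arm path.** 14 zones, 480 women, no arm effect, 2000 runs, 300 bootstrap draws of individual women within arm.

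| ICC | Rejection, equal zones | Bootstrap / true standard error | Rejection, zones of 5 to 77 (CV 0.64) |
|---|---|---|---|
| 0 | 5.6% | 0.99 | 5.5% |
| 0.01 | 9.2% | 0.86 | 12.4% |
| 0.02 | 13.0% | 0.78 | 17.8% |
| 0.05 | 24.1% | 0.61 | 30.2% |
| 0.10 | 36.8% | 0.47 | 42.4% |

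A t-test on the 14 zone means stayed between 3.7% and 5.8% throughout.

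**Step 6, the indirect effect.** This is a product of two paths, so Step 3 does not apply to it directly. It was simulated with a percentile bootstrap of women, (near-)equal zones, no arm effect, and ICC 0.01, 0.02 and 0.05.
- Standardized mediator-to-outcome slope 0.3 (1500 runs): the indirect effect was declared in 9.5%, 14.2% and 23.8% of runs, and the direct effect in 9.1%, 12.9% and 23.2%.
- Slope 0.4 (1000 runs): the indirect effect was declared in about 8%, 14% and 24%.
- Slope 0: the indirect effect was declared in at most 1.5%, below the nominal level.

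**The case against.** The strongest reply is that the fault is read into silence. The article says what SEM software can do; it does not say that women will be the resampling unit or that zones will be ignored. Resampling zones or using a cluster option is not excluded. The preceding paragraph of the same section recognizes clustering, and a condensed article may leave the estimator of a secondary model to a fuller document. These analyses are also conditional on strong power, and the sample size section already warns that mild to weak mediated effects will not be detectable, so they may never be run.

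Much of this stands. A reader might infer that the plan drops the clustering, or that its mediation standard errors are too small. The text supports neither, because the unit is not stated and the wording is permissive. A reader might also infer that every indirect effect would be declared too often; Step 6 shows that this needs a mediator that really predicts the outcome.

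Two things remain. First, the paragraph is not merely silent: it changes the model class and names one standard-error device, which in its ordinary form is wrong for a contrast between 14 zones. The earlier clustering text is tied to the GEE and does not transfer by itself. Second, the power condition is no safeguard. It mentions final sample size and variance estimates but not clustering, and a power threshold does not control false positives.

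**Conclusion.** The point holds in a limited form, as a minor one. The mediation paragraph does not carry the zone clustering over from the GEE, and the device it names would not supply it if applied to individual women.

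In that case, with ICCs of 0.01 to 0.05, the standard errors of the arm paths would be 13% to 39% too small and a 5% test would have an actual error of about 9% to 23% with equal zones, or about 11% to 28% at a size CV of 0.63. These sizes rest on assumed ICCs and an assumed CV. At ICC 0 there is no inflation. The indirect effect shares the inflation only when the mediator predicts the outcome.

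The GEE outcome analysis is not touched by this point. The figures should also not be carried over to the moderation analyses: an interaction of arm with a characteristic of the individual woman is estimated partly within zones.

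**What to change.** Add to the mediation paragraph of the Analysis section:

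1. Zone is the clustering unit in the mediation and moderation models.
2. Standard errors and intervals come from a zone-level method that allows for only 14 zones, not from resampling women. Zone-robust standard errors with a small-sample correction would do. For the arm paths, a within-pair permutation of arm is an alternative: 7 pairs give 2⁷ = 128 arrangements, so the smallest two-sided p-value is 2/128 = 0.016, and a 5% test is possible. Resampling whole zones within pairs is less attractive, because each pair holds only two zones and there are only seven pairs. Multilevel SEM is possible in principle, but the section's own worry about convergence applies to it.
3. Results are labelled exploratory.

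If a fuller analysis plan already says this, one sentence pointing to it is enough. The cost is wider intervals, fewer mediated effects declared, and some extra code. No new data are needed.
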